## Abstract

**Background:**

People living in rural Australia are more likely to die in hospital following an acute myocardial infarction than those living in major cities. While several factors, including time taken to access hospital care, contribute to this risk, it is also partially attributable to the lower uptake of evidence-based guidelines for the administration of thrombolytic drugs in rural emergency departments where up to one-third of eligible patients do not receive this life-saving intervention. Clinical pathways have the potential to link evidence to practice by integrating guidelines into local systems, but their impact has been hampered by variable implementation strategies and sub-optimal research designs. The purpose of this study is to determine the impact of a five-step clinical pathways implementation process on the timely and efficient administration of thrombolytic drugs for acute myocardial infarctions managed in rural Australian emergency departments.

**Methods/Design:**

The design is a two-arm, cluster-randomised trial with rural hospital emergency departments that treat and do not routinely transfer acute myocardial infarction patients. Six rural hospitals in the state of Victoria will participate, with three in the intervention group and three in the control group. Intervention hospitals will participate in a five-step clinical pathway implementation process: engagement of clinicians, pathway development according to local resources and systems, reminders, education, and audit and feedback. Hospitals in the control group will each receive a hard copy of Australian national guidelines for chest pain and acute myocardial infarction management. Each group will include 90 cases to give a power of 80% at 5% significance level for the two primary outcome measures: proportion of those eligible for thrombolysis receiving the drug and time to delivery of thrombolytic drug.

**Discussion:**

Improved compliance with thrombolytic guidelines via clinical pathways will increase acute myocardial infarction survival rates in rural hospitals and thereby help to reduce rural-urban mortality inequalities. Such knowledge translation has the potential to be adapted for a range of clinical problems in a wide array of settings.

**Trial registration:**

Australia New Zealand Clinical Trials Registry code ACTRN12608000209392.

## Background

Coronary heart disease is a major health problem in Australia with a reported 637,900 people diagnosed in 2004–05[1]. Acute myocardial infarction (AMI), a manifestation of coronary heart disease, is the leading cause of sudden death in the Australian population accounting for one in ten deaths[1,2]

Timely and efficient delivery of thrombolytic drugs to individuals suffering an acute myocardial infarction significantly improves mortality and morbidity and is a major aim of early treatment when invasive coronary reperfusion services are not readily available[3,4]. The National Heart Foundation of Australia (NHFA) and the Cardiac Society of Australia and New Zealand (CSANZ) jointly produced clinical guidelines for the management of AMI, including the administration of thrombolytic drugs when percutaneous coronary intervention services are unavailable. These guidelines provide precise recommendations directing which patients should receive a thrombolytic drug based on presenting symptoms, electrocardiographic (ECG) findings and contraindications[5].

People living in rural Australia are more likely to die in hospital following an AMI than people in major cities[6]. Whilst there are obvious problems associated with distances people travel to access treatment, there also appears to be lower uptake of national guidelines for thrombolytic drugs in rural areas, where up to one-third of eligible patients do not receive this life-saving intervention[7]. Peak Australian bodies, including the NHFA, the Australasian College of Emergency Medicine (ACEM) and the Cardiac Society of Australia and New Zealand (CSANZ) have promoted the development of local systems to improve to uptake of national guidelines [8].

Clinical pathways are structured, locally developed multidisciplinary care plans for specific clinical problems that take into account local resources and make explicit the local system for clinicians. They are an important tool for linking evidence to practice and can enhance adherence to guidelines[9]. However, sub-optimal implementation processes and study design have compromised the quality of current evidence regarding the impact of clinical pathways on practice[10].

Active, multifaceted approaches have been shown to improve adherence to guidelines in clinical settings over passive dissemination strategies. Active approaches include a combination of audit and feedback, reminder systems, engaging clinicians and targeted education[11,12].

The aim of this cluster randomised controlled trial is to measure the impact of a multifaceted process of clinical pathways implementation on thrombolytic delivery for AMIs managed in rural emergency departments in Australia.

## Methods

The "Acute myocardial infarction: investigating evidence-based practice to address the rural disadvantage" study is being coordinated by the Monash University School of Rural Health with rural hospitals in the state of Victoria. In this setting, all hospitals outside of major cities are categorised as rural [1]. The study is funded by a Faculty Strategic Grant from the Faculty of Medicine, Nursing and Health Sciences at Monash University and was registered with the Australia New Zealand Clinical Trials Registry (code: 12608000209392) in April 2008.

Ethics approval has been obtained from the Monash University Standing Committee on Ethics involving Humans and relevant hospital human research ethics committees. Individual informed consent is not feasible within this research design and the decision to undertake the research is the responsibility of participating institutions.

### Aim

To determine if a five-step implementation process of clinical pathways for AMI improves the proportion of patients receiving a thrombolytic drug and reduces the average time from presentation at hospital to thrombolytic administration in rural emergency departments.

### Objectives

1. To assess performance of rural hospitals against NHFA recommendations for administration of thrombolytic drugs for AMI; and

2. To measure the effect of a five step intervention for the implementation of clinical pathways in rural hospitals for AMI on:

a) the proportion of eligible patients receiving a thrombolytic drug, and

b) the time from presentation at hospital to administration of a thrombolytic drug.

### Study Design

A randomised controlled trial will be conducted involving six rural hospitals that treat and do not routinely transfer AMI patients. As displayed in table 1, pairs of hospitals were matched according to the anticipated number of eligible patients and on the basis of geographical separation in order to minimise the risk of a control hospital being influenced by procedures at an intervention hospital. Randomisation within pairs to either the intervention (n = 3) or control (n = 3) groups occurred by a simple coin toss.

**Table 1 T1:** Geographic characteristics and anticipated number of patients per site.

	**Kilometres between matched hospitals^a^**	**Mean number of eligible patients per year^b^**
Intervention Control	318	60 55

Intervention Control	463	50 50

Intervention Control	155	15 20

^a ^Source: Google Earth

^b ^Estimates based on previous research [7]

### Sample size

A 20 minute reduction in time to thrombolytic administration represents a modest improvement[7]. A total post intervention sample size of 90 patients is required to detect a 20 minute reduction in thrombolytic delivery time and a 10% improvement in eligible patients receiving thrombolysis (significance level of 5%, power of 0.8, and intra-cluster correlation coefficient of 0.283)[13]. Based on anticipated total attendance rates (i.e. 125 eligible case per annum in each condition) there will be nine months of pre and nine months of post intervention data collected.

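### The Methods give 90 patients in total as the post-intervention sample size, the Abstract gives 90 per group; the target and its power statement must be reconciled

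*Protocol article*

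**What the plan says.** The target appears twice in the protocol article.

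- **Methods, Sample size:** "A total post intervention sample size of 90 patients is required". The sentence ties this to two effects, "to detect a 20 minute reduction in thrombolytic delivery time" and "a 10% improvement in eligible patients receiving thrombolysis", with "significance level of 5%, power of 0.8, and intra-cluster correlation coefficient of 0.283".
- **Abstract, Methods/Design:** "Each group will include 90 cases to give a power of 80% at 5% significance level for the two primary outcome measures".

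The Sample size section then derives the collection period from anticipated attendance, "125 eligible case per annum in each condition", and sets nine months before and nine months after the intervention. Table 1 (Study Design) lists the expected annual numbers by hospital, three hospitals in each arm.

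**The concern.** The word *total* in the Methods, with no mention of a group, reads as the number for the whole trial. The Abstract's figure is per group. For two groups that is 90 against 180, a factor of two, with power, significance level and outcomes unchanged. One design cannot have both figures as its requirement.

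At stake is the reference figure itself. A reader who later asks whether the trial reached its planned size, or tries to check the power claim, has two targets. The article does not give the standard deviation or baseline proportion that would show by back-calculation which was meant.

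**Working it through.** **1. Can either figure be reproduced?**

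*Time outcome.* The difference is 20 minutes and the SD is not stated, so no sample size can be derived.

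*Proportion outcome.* The baseline is not stated as an input. As an assumption I take two-thirds treated, because the Background says that "up to one-third of eligible patients do not receive this life-saving intervention" (an upper bound on the untreated share), and I read the 10% as 10 percentage points. Ignoring clustering, two-sided 5%, 80% power:

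n per group = [1.96·√(2·p̄·(1−p̄)) + 0.842·√(p1(1−p1) + p2(1−p2))]² / (p2−p1)²

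With p1 = 0.667, p2 = 0.767 and p̄ = 0.717: (1.249 + 0.533)² / 0.01 ≈ 318 per group. For other baselines: 0.60 gives 356, 0.80 gives 199, 0.85 gives 141, and 0.89 gives 88. Before any allowance for clustering, 90 per group therefore needs a baseline near 0.89. Neither reading reproduces from what is stated.

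**2. Which figure fits the accrual?** (Table 1 and Sample size)

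- Intervention: 60 + 50 + 15 = 125 a year. Control: 55 + 50 + 20 = 125 a year.
- Nine months: 125 × 9/12 = 93.75 eligible per group, 187.5 in total.
- Time to reach 90 per group: 90/125 × 12 = 8.64 months.
- Time to reach 90 in total: 90/250 × 12 = 4.32 months.

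The nine-month window matches 90 per group. It is about twice what a total of 90 would need.

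**3. Does the choice change the power under the stated design?**

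Inputs: ICC 0.283 (Sample size), assumed to apply to each outcome; three hospitals per arm (Study Design), taken as equal in size. Design effect DE = 1 + (m − 1) × 0.283, where m is patients per hospital; effective n = n/DE.

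| | 45 per group | 90 per group |
|---|---|---|
| m | 15 | 30 |
| DE | 1 + 14 × 0.283 = 4.96 | 1 + 29 × 0.283 = 9.21 |
| Effective n per arm | 45/4.96 = 9.1 | 90/9.21 = 9.8 |
| Largest SD for 80% power at 20 min, 20/[2.80·√(2/n_eff)] | 15.2 min | 15.8 min |
| Power, 0.667 to 0.767 | 6.7% | 7.0% |

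Over baselines of 0.60 to 0.85, power for a 10-point gain runs from about 6% to 11% under both readings. However many patients are added, effective n per arm cannot exceed 3/0.283 = 10.6. Splitting patients in the intervention hospitals' 60:50:15 ratio lowers the effective n to about 7.7 and 8.2.

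These figures are for an unadjusted post-intervention comparison using the normal approximation. The article states no gain from pairing or baseline adjustment, so none is credited.

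**The case against.** The best defence is that *total* means the total over one arm's three hospitals. The very next sentence uses the word that way, for the attendance figure of 125 in each condition. On that usage the Methods and the Abstract agree, and the accrual supports it. I think this is probably what was meant. But the attendance sentence adds the qualifier and the sample size sentence does not, so the text still needs correcting. That an article condenses a fuller protocol does not help either: condensing explains omissions, not two values for one quantity.

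The accrual match also has a limit. It holds for eligible cases. Time to thrombolysis exists only for treated patients (Data Collection), and at an assumed two-thirds treated, nine months gives 93.75 × 2/3 = 62.5 per group, or 125 in total. For that outcome the window reaches 90 in total but not 90 per group. The accrual is therefore good evidence for the per-group reading, not proof.

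Two stronger readings are tempting, and the documents support neither.

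- *The trial could stop at 90 patients with half the data.* The post-intervention period is set by calendar at nine months, and no rule ends collection at a count.
- *The two figures give very different power.* Ignoring clustering they do: the largest workable SD is about 34 minutes at 45 per group and 48 at 90 per group, and power from two-thirds is about 18% and 32%. Those numbers leave out the protocol's own ICC. With it, the readings are nearly equivalent.

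**Conclusion.** The point holds as an inconsistency in the stated target: 90 against 180 patients for the same power, level and outcomes. That rests on the text alone. That the Methods wording is the one in error is probable, on the accrual of about 94 eligible patients per group and the neighbouring use of *total*, but it is an inference.

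The consequence is confined to the target and the power statement; planned duration and expected data are unaffected. Nor does settling the figure justify the stated 80%. With ICC 0.283 and three equal hospitals per arm, effective n is about 9 to 10 per arm either way. For the 10-point gain, power is far below 80% across the assumed baselines of 0.60 to 0.85. For the 20-minute difference, the claim would need an SD of no more than about 15 to 16 minutes. These size statements depend on the assumptions given with the calculations; the contradiction does not.

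**What to change.** In the Sample size section, state the target as 90 eligible patients per group (180 in total) in the post-intervention period. If 90 in total was truly intended, correct the Abstract instead and explain the nine-month window.

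Then restate the power for the chosen number with ICC 0.283 and three hospitals per arm. Give the SD assumed for time to thrombolysis and the baseline proportion assumed for treatment, and say whether the 10% is absolute or relative. Any gain counted on from matching or baseline adjustment should be shown. For the time outcome, state whether the 90 counts eligible or treated patients.

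The wording change costs one sentence. Restating the power costs a short recalculation and needs the original inputs, which the article does not give. Neither alters the planned data collection.

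### The stated 80% power cannot hold for the proportion treated, nor jointly for both primary outcomes, with three hospitals per group and an ICC of 0.283; for time it cannot be checked

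*Protocol article*

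**What the plan says.** The Sample size section sets the post-intervention sample at 90 for two targets, a 20-minute reduction in time to thrombolysis and a 10% improvement in the proportion of eligible patients treated, with "significance level of 5%, power of 0.8, and intra-cluster correlation coefficient of 0.283". The abstract (Methods/Design) repeats the claim: "Each group will include 90 cases to give a power of 80% at 5% significance level for the two primary outcome measures".

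The two places count differently. The abstract has 90 per group, whereas the Sample size section reads "A total post intervention sample size of 90 patients is required".

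The Study Design section fixes the number of clusters: "Randomisation within pairs to either the intervention (n = 3) or control (n = 3) groups occurred by a simple coin toss". The Sample size section gives no control-group proportion and no SD for time, and does not say which outcome the ICC belongs to. The only figure that bears on the control rate is in the Background, where "up to one-third of eligible patients do not receive this life-saving intervention".

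**The concern.** An ICC of 0.283 is large, and three clusters per group is very few. When hospitals differ that much, further patients from the same three hospitals add little information, so 90 patients per group cannot act like 90 independent patients. The document prints the ICC, the sample size, the number of hospitals and the power together, so whether they agree can be checked from the text.

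What is at stake is how the result is read. The Discussion presents the trial as a rigorous test of an intervention whose evidence is inconclusive. If the true power for the proportion is far below 80%, a non-significant result is likely even when the pathway achieves its full target, and a reader who trusts the stated power could take that result as evidence against pathways.

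**Working it through.** **Inputs**
- ICC 0.283, 5% significance, stated power 0.80 (Sample size). Sidedness is not stated; two-sided is assumed unless noted.
- 90 per group (abstract), three hospitals per group (abstract, Study Design), so m = 30 per hospital.
- Expected accrual: 125 × 9/12 = 93.75 per group (Sample size), which fits the per-group reading.
- Gain of 10%, read as 10 percentage points. The relative reading (67% to 73%) is harder to detect.
- Control rate 67%: an assumption, from at most one-third untreated in the Background. Range tried: 50% to 90%. At 90% a 10-point gain means that practically every intervention patient is treated.

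**Step 1. Can the stated figure be reproduced without clustering?**
n per group = (1.96 + 0.84)² × [p₁(1−p₁) + p₂(1−p₂)] / 0.10². For 66.7% versus 76.7% the bracket is 0.222 + 0.179 = 0.401, so n ≈ 315 (318 with the pooled null variance). With 90 per group, SE = √(0.401/90) = 0.0668 and power = Φ(0.10/0.0668 − 1.96) = Φ(−0.46) ≈ 32%. The stated figure is not reproduced.

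If clustering is ignored, 90 per group does exceed 80% at the extreme of 90% to 100% (about 87%), but not at 85% to 95% (about 61%).

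**Step 2. Apply the stated ICC.**
Design effect = 1 + (30 − 1) × 0.283 = 9.21.
Effective size = 90/9.21 = 9.8 per group.
Ceiling as m grows without limit = 3/0.283 = 10.6 per group.

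The unequal sizes in Table 1 make it slightly worse: the same calculation with size-weighted clusters gives 8.2 (intervention) and 8.7 (control).

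**Step 3. Power for the proportion, follow-up data only.**
SE = √(0.401/9.775) = 0.203, and 0.10/0.203 = 0.49.

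| Control rate | Normal approximation, pooled to unpooled variance | t, 4 df |
|---|---|---|
| 50% | 6.4–7.3% | 6.4% |
| 67% | 7.0–7.8% | 6.7% |
| 80% | 8.8–9.6% | 7.8% |
| 90% | 16.6–18.1% | 12.9% |

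A one-sided test gives about 12% at 67% and about 26% at 90%.

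**Step 4. Other reading of 90.**
If 90 is the total, there are 45 per group and m = 15. The design effect is 1 + 14 × 0.283 = 4.96, the effective size is 45/4.96 = 9.1 and power at 67% is about 7%.

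**Step 5. Most favourable use of the baseline period.**
Assume that hospital effects are perfectly correlated between the two nine-month periods and that the analysis adjusts for each hospital's baseline. The correlation of hospital summaries is r = 30 × 0.283/9.21 = 0.922. The effective size becomes 9.775/(1 − 0.922²) = 65.3. Two-sided power (pooled variance) is then about 24% at 67%, 36% at 80% and 75% at 90%. With a between-period correlation of 0.8 in place of 1, it is 11%, 15% and 32%.

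**Step 6. Time to thrombolysis.**
The largest patient SD compatible with 80% power for 20 minutes is 20/[(1.96 + 0.84) × √(2/9.775)] = 15.8 minutes. With t on 4 df the required non-centrality is 3.77, giving 20/[3.77 × √(2/9.775)] = 11.7 minutes. If the SD were 30, 40 or 50 minutes (illustrative values that are not in the document), power would be about 31%, 20% or 14% by the normal approximation.

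**Step 7. Expected precision.**
The 95% CI half-width for 67% versus 77%, unadjusted, is 1.96 × 0.203 = 40 points, or 2.776 × 0.203 = 56 points with t on 4 df.

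**The case against.** Several limits on this point stand.

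- **Time.** A reader might infer that the power claim fails for both outcomes. The document does not support that. Without an SD, 80% for time can be neither confirmed nor refuted, and the ICC is not tied to a named outcome. The joint claim still fails, because the abstract asserts 80% for both.
- **The control rate.** A reader might take 7% as the power of the trial. It rests on 67% treated, which comes from background text that says up to one-third are untreated, so the true rate may be higher. The range should be quoted.
- **Baseline data.** Nine months of pre-intervention data are planned, and the Data Analysis section promises between-group comparisons that allow for clustering, without giving a model. Follow-up-only power is therefore not an upper limit. Step 5 shows that the best two-sided case still falls short of 80%.
- **Sidedness.** Because it is not stated, one extreme remains: a one-sided test, perfect between-period correlation and 90% rising to about 100%. There SE = √(0.09/65.3) = 0.037 and power = Φ(0.10/0.037 − 1.645), about 85%; with t on 4 df it drops to about 71%. Nothing in the document suggests that these conditions were assumed.

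Other inferences go too far. A minimum detectable difference derived from the effective size would exceed the 33 points available above a 67% control rate, so it has no meaning here. With three pairs, a pair-respecting randomisation test cannot give a two-sided p below 2/8, but Data Analysis plans no such test, so this says nothing about the stated power. Finally, 318 × 0.283 = 90, which may suggest that the ICC was used as a multiplier in place of the design effect. The article does not show its calculation, so that is conjecture.

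Condensation into a journal article does not explain the conflict, because the figures that disagree are all printed.

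**Conclusion.** The power statement is wrong as written. For the proportion treated, 80% two-sided power is not attainable with three hospitals per group and an ICC of 0.283 under either reading of 90, at any control rate from 50% to 90%, with or without the baseline data. A follow-up-only comparison has about 7–8% power at an assumed 67% control rate and about 6–18% across the range. The joint claim for both primary outcomes falls with it. For time the claim is unverifiable and holds only if the patient SD is at most about 16 minutes (normal approximation) or 12 minutes (t, 4 df).

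The conclusion rests on 10% meaning percentage points, a two-sided 5% test, roughly equal hospital sizes, and the stated ICC applying to the proportion. Table 1's unequal sizes, or a relative 10%, would lower the power.

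**What to change.** In the abstract and the Sample size section:

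1. Withdraw the 80% power claim, or restate it with its assumptions.
2. Reconcile 90 per group with a total of 90.
3. State the control proportion and the SD assumed, whether the test is one- or two-sided, and which outcome the ICC refers to.
4. Report the design effect (about 9), the effective size (about 10 per group) and the resulting power, saying whether it is follow-up-only or baseline-adjusted.
5. Give the expected 95% CI half-width for the proportion (about 40–56 points for 67% versus 77%, unadjusted).
6. Note that a non-significant result would not be evidence of no effect.

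Presenting the trial mainly as estimation would fit these figures, but that is a reporting choice and the correction does not depend on it.

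The cost is wording only, with no added hospitals or patients. The downside is a far less favourable power statement.
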